1.0 Background and Rationale

2.0 Study Objectives

3.0 Subject Eligibility

4.0 Treatment Plan

5.0 Study Procedures

6.0 Data Safety Monitoring Plan

7.0 Data Collection

8.0 Quality of Life

9.0 Quality of Life and Cost Effectiveness

10.0 Statistical Considerations

References

**STUDY SCHEMA**[figure not shown]

Number of patients = Minimum: 17, Maximum: 48

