**Phase I**

Patients in each dose cohort will all be treated as a single group for fraction reduction. The starting dose will be 3.33 Gy per fraction for 15 fractions (total dose = 50 Gy). Subsequent cohorts of patients will receive a biologically equivalent dose delivered in 5 fewer fractions per step. If significant toxicity is encountered at the starting dose, an increase in fraction step will occur (step -1) to 3.28 Gy per fraction for 16 fractions (total dose 55 Gy).

| Step No. | Fractions | Dose per fraction (Gy) | Total Dose (Gy) | No. Patients |
|-----------------|------------------|-------------------------------|------------------------|---------------------|
| -1              | 16               | 3.28                          | 52.5                   | 3                   |
| 0 (starting)    | 15               | 3.33                          | 50.0                   | 3-15                |
| 1               | 10               | 4.50                          | 45.0                   | 7-15                |
| 2               | 5                | 8.50                          | 42.5                   | 7-15                |

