## 10.2 Phase 1 waiting periods

Fraction reduction for this phase 1 clinical trial will not occur until sufficient waiting has occurred after a cohort has been treated. A period of 90 days must pass before further fraction reduction for the purpose of assessing toxicity. If 90 days have passed without a DLT at a dose level, the trial will be allowed to the next level, so long as either criteria for defining the MTD or criteria for further fraction reduction is not reached. If the maximum number of patients are enrolled to a given fraction level, yet criteria for follow-up is not reached in a representative sample of patients, further enrollment to the protocol will be suspended until adequate follow-up is reached. No action will be taken for Grade 1 or Grade 2 toxicities. If any 2 Grade 3 toxicities occur within a dose level likely or definitely related to radiation therapy, the trial will be terminated with reporting of DLT at that dose level. Any Grade 4 or Grade 5 toxicity found to be likely or definitely related to treatment will result in termination of the trial with reporting of DLT at that dose level.

Grade 3 toxicities likely or definitely related to protocol therapy will result in action in schema provided below:

[figure not shown]

For level -1, if a Grade 3 toxicity occurs, the trial will be terminated with reporting of DLT.

For level 0, if a Grade 3 toxicity occurs, a step de-escalation will occur to level -1. If no grade 3 toxicities are experienced at level 0, the trial will proceed to level 1.

---

For level 1, if there are no Grade 3 toxicities after initial enrollment of 7 patients, an additional 8 patients will be enrolled. If there is no grade 3 toxicity after enrollment of an additional 8 patients, the trial will proceed to level 2. If there is a 1 grade 3 toxicity in the additional 8 patients, the trial will proceed to level 2 at the discretion of the PI and DSMC.

For level 1, if there is 1 Grade 3 in the initial 7 patient cohort, an additional 8 patients will be enrolled. If there is an additional Grade 3 toxicity at this level, the trial will be terminated with reporting of DLT. If there are no further grade 3 toxicities in the additional 8 patients, proceeding to the next level will be done at discretion of the DSMC and PI.

For level 1, if there are 2 grade 3 toxicities in the initial 7 patient cohort, the trial will be terminated with reporting of DLT.

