For level 2, if there are 0 grade 3 toxicities in the initial 7 patient cohort, the trial will enroll an additional 8 patients.

For level 2, if there is 1 grade 3 toxicity in the initial 7 patient cohort, the trial will enroll an additional 8 patients. If there is another grade 3 toxicity, the trial will be terminated with reporting of DLT.

For level 2, if there are 2 grade 3 toxicities in the initial 7 patient cohort, the trial will be terminated with reporting of DLT.

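### The stated minimum of 17 patients conflicts with the section 10.2 rules, under which a trial that tolerates level 2 enrols at least 33

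*Protocol*

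**What the plan says.** The only overall size statement is in the Study Schema: "Number of patients = Minimum: 17, Maximum: 48". The Phase I table beneath it gives 3 patients for level -1, 3-15 for level 0, and 7-15 for each of levels 1 and 2. The dose-escalation table in section 4.1 lists 3, 3, 7 and 7 as minimum numbers. Section 10.1 speaks of cohorts of 3-15.

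Section 10.2 says what happens at each level:

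- Level 0: any grade 3 event leads to level -1; otherwise "If no grade 3 toxicities are experienced at level 0, the trial will proceed to level 1". No number of patients is attached to this rule.
- Level 1: "For level 1, if there are no Grade 3 toxicities after initial enrollment of 7 patients, an additional 8 patients will be enrolled". One event in the first 7 also leads to 8 more patients, and two events end the trial.
- Level 2: "For level 2, if there are 0 grade 3 toxicities in the initial 7 patient cohort, the trial will enroll an additional 8 patients". Again, one event leads to 8 more patients and two events end the trial.
- Level -1: a grade 3 event ends the trial. The text does not say what follows if there is none.
- Any level: two related grade 3 events, or any related grade 4 or 5 event, end the trial.

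Section 4.13 sets a different condition for leaving level 1: 7 patients observed for 90 days. For levels -1 and 0 it asks for three observed patients before accrual to the next higher level.

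**The concern.** A minimum of 17 tells the reader that the trial can run through all three levels with 7 patients at each of levels 1 and 2. Under section 10.2, 7 is only an interim look at those levels. Every outcome at 7 either expands the level to 15 or stops the trial.

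The size statement is what ethics, monitoring and resource decisions rest on. If level 2 is to be declared tolerated, the true requirement is nearly double the stated minimum. If 17 is read as a guaranteed lower limit, it hides the fact that the trial may end on far fewer patients.

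The unclear use of 3-15 at level 0 also matters. If level 1 is terminated, level 0 is what remains as tolerated, and the visible text does not settle whether that rests on 3 patients or on as many as 15.

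**Working it through.** **Inputs.** Level sizes come from the Phase I table: level -1, 3; level 0, 3-15; level 1, 7-15; level 2, 7-15. Decision rules come from section 10.2. The waiting rule comes from section 4.13. Replacements are left out.

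**Step 1: reproduce the stated figures.**

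- Minimum: lower limits of levels 0, 1 and 2 = 3 + 7 + 7 = 17.
- Maximum: upper limits of levels -1, 0, 1 and 2 = 3 + 15 + 15 + 15 = 48.

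Both match exactly, so both are sums of table limits.

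**Step 2: apply section 10.2 to levels 1 and 2.**

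| Grade 3 events in first 7 | Action | Patients at that level |
|---|---|---|
| 0 | add 8 | 15 |
| 1 | add 8 | 15 |
| 2 | terminate | 7 |

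A level found tolerable has 7 + 8 = 15 patients. The smallest trial in which level 2 is tolerated is therefore 3 + 15 + 15 = 33. With level 0 filled to 15 it is 15 + 15 + 15 = 45.

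**Step 3: early endings.** With 3 patients at level 0 and whole cohorts counted:

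| Ending | Total |
|---|---|
| Two grade 3 events at level 0 (general rule) | 3 |
| One event at level 0, then an event at level -1 | 3 + 3 = 6 |
| Two events in the first 7 at level 1 | 3 + 7 = 10 |
| Second event in the level 1 expansion | 3 + 15 = 18 |
| Two events in the first 7 at level 2 | 3 + 15 + 7 = 25 |
| Second event in the level 2 expansion | 3 + 15 + 15 = 33 |

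The total 17 is not in this list. A related grade 4 or 5 event can end the trial at any patient.

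**Step 4: does the waiting rule in section 4.13 rescue 17?** If level 2 opens after 7 patients at level 1, a tolerated level 2 gives 3 + 7 + 15 = 25. The total is 3 + 7 + 7 = 17 only when level 2 is terminated at its first 7. That is neither the size of a trial that tolerates level 2 nor the floor.

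**Step 5: the maximum.** Reaching 48 takes 15 patients at level 0, a grade 3 event there, 3 patients at level -1, and then 15 at each of levels 1 and 2. The visible text of 10.2 gives no trigger for patients 4-15 at level 0 and no upward step from a clean level -1. Section 4.13 only implies such a step. Through level -1 with 3 patients at level 0, the total is 3 + 3 + 15 + 15 = 36, or 39 if level 0 is re-entered with 3 new patients. None of these totals exceeds 48.

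**Step 6: what level 0 would support.** With no event in n patients, the one-sided 95% upper limit for the event rate is 1 - 0.05^(1/n). For n = 3 this is 0.63; for n = 15 it is 0.18. The 95% level is chosen here, since the protocol sets none.

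**The case against.** Both figures have a plain source, the Phase I table, and 7 is a true size for an initial cohort. The minimum column in 4.1 can be read that way, and section 4.13 is a written source for 7 at level 1. Section 10.1 also counts reaching the MTD as completion, so a trial ending after 7 patients at level 1 or 2 has completed in the protocol's own sense. All of this stands, and it is why the point is worded as a trial in which level 2 is tolerated. It does not rescue 17, which is not the smallest MTD ending either.

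A reader might go further and infer that 33 is the only size at which the trial can finish, or that 48 is 15 too many. The document does not support this. Section 10.2 attaches no number to the level 0 rule. The 3 at level 0 is a floor wherever it appears. The Phase I table and section 10.1 allow up to 15, and section 10.2 foresees a level filling to its maximum while follow-up is awaited. So 33 is the lower end of a range reaching 45 without level -1, and 48 is a valid ceiling.

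The figure in section 10.2 was not available for this check and may hold further branches for level 0 or level -1. The statement that no rule covers those branches therefore applies to the text only. The written rules for levels 1 and 2 are explicit and are enough to defeat 17.

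**Conclusion.** The minimum of 17 is wrong as stated. Under section 10.2 as written, a trial in which level 2 is tolerated enrols 33 to 45 patients, before replacements and any level -1 patients. The stated minimum is 16 short of the lower end (33 - 17). As a floor for any ending, 17 is too high, since whole-cohort stops can fall at 6 or 10 patients and a related grade 4 or 5 event can come sooner. If the waiting rule in 4.13 governed instead, the lower end would be 25, still not 17.

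The maximum of 48 is not shown to be wrong. What is open there is how patients 4-15 enter level 0 and what follows a clean level -1, subject to the missing figure.

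A reader might also infer that the precision of the 5-year control and survival estimates is undermined. The protocol states no precision target for those outcomes, so that does not follow.

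The counts assume whole cohorts, 3 patients at level 0 for the lower figure, and a decision to proceed wherever 10.2 leaves it to the PI and the DSMC.

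**What to change.** In the Study Schema, restate the minimum as 33 for a trial in which level 2 is tolerated under section 10.2, note that replacements and any level -1 patients come on top, and keep 48 as the ceiling. A flat size of 33 should not replace the range, because the table allows up to 45 without level -1. Give the early-stopping totals separately, and say that a related grade 4 or 5 event can end the trial at any point.

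Then reconcile the passages that disagree:

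- Sections 4.13 and 10.2 differ on what must happen at level 1 before level 2 opens (7 observed against 15 enrolled). The sponsor must settle which applies. If it is the former, the restated minimum must be recomputed.
- The lower limits of 7 in the Phase I table and in 4.1 should be labelled as initial cohort sizes, or changed to agree with 10.2.
- The use of 3-15 at level 0, and what follows a clean level -1, should be stated in the text of 10.2 so that they agree with the table and 4.13.

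This costs a correction of text and tables. The only unwelcome effect is a larger stated minimum.

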**Phase I**

Patients in each dose cohort will all be treated as a single group for fraction reduction. The starting dose will be 3.33 Gy per fraction for 15 fractions (total dose = 50 Gy). Subsequent cohorts of patients will receive a biologically equivalent dose delivered in 5 fewer fractions per step. If significant toxicity is encountered at the starting dose, an increase in fraction step will occur (step -1) to 3.28 Gy per fraction for 16 fractions (total dose 55 Gy).

| Step No. | Fractions | Dose per fraction (Gy) | Total Dose (Gy) | No. Patients |
|-----------------|------------------|-------------------------------|------------------------|---------------------|
| -1              | 16               | 3.28                          | 52.5                   | 3                   |
| 0 (starting)    | 15               | 3.33                          | 50.0                   | 3-15                |
| 1               | 10               | 4.50                          | 45.0                   | 7-15                |
| 2               | 5                | 8.50                          | 42.5                   | 7-15                |

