## 4.0 TREATMENT PLAN

### 4.1 Treatment Dosage and Administration

- 4.1.1 This phase I clinical trial will begin with hemilarynx CyberKnife radiotherapy to a dose of 50 Gy delivered in 15 fractions. If this dose/fraction scheme has no dose limiting toxicity, there will be a reduction to 10 fractions to a bio-equivalent dose of 45 Gy. If this dose level is tolerated without dose limiting toxicity, there will be an additional reduction to 5 fractions to a bio-equivalent dose of 42.5 Gy. The patients will also be followed prospectively for voice quality and quality of life. The dose will be prescribed to provide at least 95% planning treatment volume (PTV) coverage.

| Agent         | Pre-medications;
Precautions                                                             | Dose | Route | Schedule                                |
|---------------|---------------------------------------------------------------------------------------------|------|-------|-----------------------------------------|
| Dexamethasone | Pre-medicate with Dexamethasone 1 hour prior to radiation treatments for dose level 1 and 2 | 4 mg | Oral  | Daily 1 hour prior to radiation therapy |

| Dose-Escalation Schedule |                                                                                     |                            |
|--------------------------|-------------------------------------------------------------------------------------|----------------------------|
| Dose Level               | Dose of the Study Agent(s)*                                                         | Minimum Number of Patients |
| Level -1                 | 52.5 Gy in 16 fractions of 3.28 Gy per fraction daily                               | 3                          |
| Level 0                  | 50 Gy in 15 fractions of 3.33 Gy per fraction daily, delivered 5 fractions per week | 3                          |
| Level 1                  | 45 Gy in 10 fractions of 4.5 Gy per fraction daily, delivered 3 fractions per week  | 7                          |
| Level 2                  | 42.5 Gy in 5 fractions of 8.5 Gy per fraction daily, delivered 2 fractions per week | 7                          |

| Toxicity Dose Reductions                                                                                    |                                                               |

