#### **4.13 Subject Replacement**

Three subjects within dose levels -1 and 0 must be observed for 90 days before accrual to the next higher dose level may begin. For level 1, 7 patients must be observed for 90 days before accrual to the next higher dose level. If a subject is withdrawn from the study prior to completing therapy without experiencing a dose limiting toxicity prior to withdrawal, an additional subject may be added to that dose level. Subjects missing 3 or more radiation treatments due to toxicity will not be replaced since these subjects will be considered to have experienced a dose limiting toxicity.

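### Level -1 is given two total doses (55 and 52.5 Gy), and the move to it after toxicity at level 0 is called a de-escalation although its total dose is higher than level 0's

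*Protocol*

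**What the plan says.** The Phase I part of the Study Schema sets the starting level (level 0): "The starting dose will be 3.33 Gy per fraction for 15 fractions (total dose = 50 Gy". Section 4.1 repeats it: "50 Gy in 15 fractions of 3.33 Gy per fraction daily, delivered 5 fractions per week".

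The schema text then gives the fall-back. The trigger is "If significant toxicity is encountered at the starting dose", and the action is "an increase in fraction step will occur (step -1) to 3.28 Gy per fraction for 16 fractions (total dose 55 Gy". The table directly below that text lists step -1 with the same 16 fractions and 3.28 Gy but a total of 52.5 Gy. Section 4.1 agrees with the table: "52.5 Gy in 16 fractions of 3.28 Gy per fraction daily".

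Section 10.2 states the rule as it would be applied: "For level 0, if a Grade 3 toxicity occurs, a step de-escalation will occur to level -1". It adds that a Grade 3 toxicity at level -1 ends the trial with a dose-limiting toxicity reported.

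Section 1.4 cites European experience with 16-fraction courses totalling 50 to 52.5 Gy as the background for the starting level. The protocol states no alpha/beta ratio, no biologically effective dose for any level and no correction for overall treatment time.

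**The concern.** There are two faults, and both can be seen from the printed figures.

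First, a prescription total appears with two values for one level. A reader of the schema text and a reader of Section 4.1 would record different totals for the same fractionation.

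Second, the level used after a patient has had a Grade 3 toxicity is labelled a step down, yet it has one more fraction of nearly the same size and so a larger total dose. Patients would enter it because level 0 had caused toxicity. If a Grade 3 event then occurred at level -1, the trial would end without a less intense course having been tried. If none occurred, the report could describe tolerance after de-escalation, which the dose figures would not support. This affects both patient safety and what a level -1 result can show.

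**Working it through.** **Inputs.** Fractions (n) and dose per fraction (d) come from the Phase I schema and the Section 4.1 table. Level -1 is n = 16, d = 3.28 Gy. Level 0 is n = 15, d = 3.33 Gy. The alpha/beta ratio is not in the protocol, so I assume a range of 2 to 20 Gy.

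**Step 1: reproduce the stated totals (n × d).**
- Level 0: 15 × 3.33 = 49.95 Gy. The stated 50 Gy reproduces.
- Level -1: 16 × 3.28 = 52.48 Gy. The 52.5 Gy in both tables reproduces. The 55 Gy in the schema text does not; it is about 2.5 Gy too high.
- To reach 55 Gy would take 55/16 = 3.44 Gy per fraction, or 55/3.28 = 16.8 fractions. Neither is stated anywhere.

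**Step 2: compare level -1 with level 0.**
- Total dose: 52.48 − 49.95 = 2.53 Gy more, and 52.48/49.95 = 1.051, or +5.1%. The text's 55 Gy would be +10% on 50 Gy.
- Fraction size: (3.33 − 3.28)/3.33 = 1.5% smaller.
- Where the difference comes from: the smaller fraction saves 15 × 0.05 = 0.75 Gy over the first 15 fractions, and the sixteenth adds 3.28 Gy. The net is 3.28 − 0.75 = 2.53 Gy more.

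**Step 3: allow for fraction size.** In the linear-quadratic model without a time factor, BED = n·d + n·d²/(alpha/beta). The two parts are:
- n·d: 52.48 v 49.95 (+5.1%)
- n·d²: 16 × 3.28² = 172.1 v 15 × 3.33² = 166.3 (+3.5%)

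Both parts are larger at level -1, so its BED is larger at every alpha/beta, and the excess must lie between 3.5% and 5.1%.

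| Assumed alpha/beta (Gy) | BED, level -1 | BED, level 0 | Difference |
|---|---|---|---|
| 2 | 138.55 | 133.12 | +4.1% |
| 3 | 109.86 | 105.39 | +4.2% |
| 5 | 86.91 | 83.22 | +4.4% |
| 10 | 69.69 | 66.58 | +4.7% |
| 20 | 61.09 | 58.27 | +4.8% |

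Using exactly 50/15 Gy per fraction for level 0 instead of the rounded 3.33 gives +3.9% at alpha/beta 2 and +4.7% at 20.

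**Step 4: could overall time reverse this?** Suppose the sixteenth fraction falls after a weekend and adds 3 days (an assumption). Cancelling the BED gap would then need (69.69 − 66.58)/3 = 1.0 Gy per day at alpha/beta 10, or (109.86 − 105.39)/3 = 1.5 Gy per day at alpha/beta 3. The protocol invokes no time factor.

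**The case against.** The best defence is that the protocol orders its levels by number of fractions and not by total dose. Levels 1 and 2 have lower totals (45 and 42.5 Gy) and are still the more demanding steps, and the Section 10.1 endpoint is the smallest tolerated number of fractions. On that axis the order is intact: fractions run 16, 15, 10, 5 and fraction sizes 3.28, 3.33, 4.5, 8.5 Gy. Level -1 also matches the upper end of the 16-fraction experience that Section 1.4 regards as safe. And 55 Gy is probably a slip, since both tables agree on 52.5 Gy.

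Much of this stands. It would be wrong to say that the whole ordering of levels is broken, that level -1 is an untried schedule, or that 55 Gy is a course anyone intended. But a 1.5% smaller fraction does not offset a 5.1% larger total, and a precedent for a schedule does not make it less intense than the level that has just caused toxicity.

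A reader might also infer more than the documents support:
- *That Section 10.2 has no path after a clean level -1, or that patients return to level 0.* The Section 10.2 schema is a figure not reproduced in the text available and may contain that branch. The Section 4.13 sentence, "Three subjects within dose levels -1 and 0 must be observed for 90 days before accrual to the next higher dose level may begin", is a waiting rule and does not route patients.
- *That the claim of biological equivalence fails.* That statement, "Subsequent cohorts of patients will receive a biologically equivalent dose delivered in 5 fewer fractions per step", concerns the steps with fewer fractions, not level -1. Testing it at 8.5 Gy per fraction would rest on an assumed alpha/beta and on extending the linear-quadratic model to a range where Section 1.2 itself cautions against conventional radiobiology. It is a separate question.
- *How often the fall-back would be used.* The protocol gives no Grade 3 rate for level 0, and Section 10.2 ends the trial after two related Grade 3 events within a level, so no reliable probability follows.

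**Conclusion.** The point holds in two parts. The 55 Gy in the schema text is contradicted by its own fractions and fraction size (52.48 Gy) and by both dose tables (52.5 Gy). The label in Section 10.2 is contradicted by the dose figures: level -1 exceeds level 0 by 2.53 Gy in total dose (+5.1%).

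The first part and the total-dose comparison rest only on printed numbers. The statement about biologically effective dose rests on the linear-quadratic model with no time factor. Its direction holds at any alpha/beta, and its size, about +4% to +5%, is for assumed values of 2 to 20 Gy. The two fraction sizes are almost equal, so this comparison does not stretch the model.

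The excess is modest and confined to a conditional branch listed at three patients. It still needs correcting, because it lies in the rule applied after toxicity and it prevents a level -1 result from being read as tolerance of a less intense schedule. The figures do not show that level -1 is unsafe or that it should not be used, and this review does not say so.

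**What to change.** The sponsor should:
1. Reconcile the level -1 total dose across the Phase I schema text, the table beneath it and the Section 4.1 table, so that fractions, fraction size and total agree everywhere.
2. Reconcile the term de-escalation in Section 10.2, and the stated purpose of level -1, with that level's dose figures relative to level 0. The text should say in what sense level -1 is a step down, and what a result there is meant to show.

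Which dose or clinical rule is right is for the sponsor to decide, and none is proposed here. The cost is a protocol amendment and a check by the radiation physicist. No extra patients are needed.
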